### Index test

A diagnostic criteria assessment looking for the presence or absence of each of the diagnostic features (box 1). Using the same assessment, the index test is divided into index test 1 and index test 2.

#### Index test 1

The international eDelphi consensus study agreed 16 diagnostic features of childhood psoriasis and separated them into major and minor criteria. In the consensus study, a scoring algorithm was proposed where the presence of one or more major criteria or three of more minor criteria would support a diagnosis of psoriasis. Together these 16 diagnostic features and the scoring algorithm form index test 1.^26^

#### Index test 2

Two additional features were close to reaching consensus and were emphasised as important in the feedback from the expert participants. These 18 items will be used to create the best predictive criteria using multivariate analysis. The best predictive criteria form index test 2.

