### Sample size and data analysis

The sample size is based on the primary objective. First, based on a 95% CI that the positive likelihood ratio (LR) is greater than 2 assuming a ratio of 1:1 cases to controls and an estimated sensitivity of 0.8 and specificity of 0.7 the sample size required is 74 cases and 74 controls.^27^

Second, transparent reporting of multivariable prediction models for individual prognosis or diagnosis (TRIPOD) has stated that there are no clear methods for calculating an adequate sample size. The guidance supports the current rule of thumb for sample size calculations of 10 events per variable.^28^ As there are 16 diagnostic features in the consensus agreed diagnostic criteria, a sample size of 160 cases and 160 controls has been calculated.

Participant characteristics will be analysed using descriptive statistics. The diagnostic accuracy of the consensus agreed criteria will be calculated using sensitivity and specificity; 95% CIs will be presented. Multivariate logistic regression analysis will be used to develop the best predictive criteria using the DIPSOC data. The diagnostic features will be entered into the backward regression model. All minor criteria will be entered into the regression model and LR will be presented. Variation of diagnostic accuracy in different clinical contexts will be explored in stratified analysis for the following variables; age at the time of assessment, sex, assessor type and consultation type (new or follow-up).

The results of the multivariate analysis will be plotted on a receiver operator characteristic (ROC) curve and a coefficient threshold determined. The minimum threshold for the best predictive criteria has been set at 0.8 sensitivity and 0.8 specificity after consultation with the expert advisory group (detailed in the acknowledgements). The best predictive diagnostic criteria will be applied to the study data and sensitivity and specificity calculated. The performance of the consensus agreed criteria and the best predictive model criteria will be compared using area under the ROC curve.

Interobserver variability and variability in the reference standard will be calculated using the kappa statistic. Further details on the analysis will be made public in the statistical analysis plan which will be shared on the DIPSOC website www.nottingham.ac.uk/go/dipsoc before the end of recruitment.

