### Minimising bias

We have minimised selection bias by asking sites to approach all eligible cases and consecutive controls. All those approached but not recruited will be included in a screening log to demonstrate a non-selective approach. By minimising exclusion criteria, we aimed to design an inclusive study to support generalisation of the results.

The diagnostic criteria assessment will be undertaken by an investigator who is unaware of (blinded to) the dermatologist’s diagnosis of the participant. Investigators are trained to focus on the presence or absence of each clinical feature. The study will test a prespecified scoring algorithm proposed through the eDelphi consensus study and a prespecified diagnostic threshold decided with the expert advisory group.

Bias in the reference standard will be minimised by ensuring all participants have a confirmed diagnosis by a dermatologist. As this is a case–control study, the reference standard will predate the index test. Variability in the reference standard will be examined using clinical photographs.

We have designed the study to include same day recruitment directly from clinic, therefore, the time between the reference standard and index test for most participants will be short. All participants receive the same reference standard (a dermatologist’s diagnosis), therefore, complete verification will be achieved. All participants will be included within the analysis and a complete data set sensitivity analysis is planned. Data are extracted from the medical record by an investigator who did not undertake the diagnostic criteria assessment (blinded to the index test).

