### Limitations

DIPSOC has been designed to ensure a high-quality diagnostic study, but there are some important limitations. A case–control study design is likely to overestimate the diagnostic accuracy of the criteria. DIPSOC is a development study, and therefore, this study design is appropriate and feasible for this early stage of testing. In the future, further diagnostic cohort studies are needed to test, potentially improve, and validate the resulting criteria in the setting and population they are intended to be used. Another limitation of the study design is spectrum bias. Participants recruited from paediatric dermatology clinics are likely to have more severe and persistent disease (ie, a different clinical presentation) compared with children/young people in the community who are managed by general practitioners. This spectrum bias may lead to an overestimation of the diagnostic accuracy because participants may have more obvious disease. DIPSOC recruits both new and follow-up (incident and prevalent) patients. This will include participants currently on treatment who’s skin rashes may have changed since starting treatment. However, paediatric dermatology clinics are a feasible setting to recruit the required sample size and obtain a reference standard to ensure complete verification. DIPSOC does not include external validation of the best predictive criteria and this will need to be undertaken in separate studies once the diagnostic criteria have been developed.

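### Index test 2 is selected, given its cut-off and assessed on the same 320 children, so its stated accuracy is apparent accuracy and favours it; no optimism correction is described

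*Protocol article*

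**What the plan says.** All references are to the protocol article.

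- **Candidates.** Index test, on its second part: "These 18 items will be used to create the best predictive criteria using multivariate analysis".
- **Development.** Sample size and data analysis: the criteria come from multivariable logistic regression with backward selection, fitted to the DIPSOC data.
- **Cut-off.** Same section: the model results are to be "plotted on a receiver operator characteristic (ROC) curve and a coefficient threshold determined". A minimum of 0.8 for both sensitivity and specificity was agreed with the expert advisory group.
- **Assessment.** Same section: "The best predictive diagnostic criteria will be applied to the study data and sensitivity and specificity calculated". The two index tests are then compared by area under the ROC curve.
- **Bias control.** Minimising bias lists, as a safeguard, "a prespecified diagnostic threshold decided with the expert advisory group".
- **Validation.** Limitations: "DIPSOC does not include external validation of the best predictive criteria"; that is left to separate studies. Internal validation is not mentioned in the article. Further analysis detail is deferred to a SAP, and the article is based on a longer full protocol; neither is shown.

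**The concern.** Three steps are fitted to one sample: which features stay, what weights they carry, and where the cut-off lies. Sensitivity, specificity and AUC are then computed on that sample. Each step exploits chance patterns in these particular children, so the figures will on average be better than the same frozen rule would achieve in new children from the same clinics. This is separate from the case–control and spectrum biases that the article acknowledges.

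Two stated uses of the figures are affected. The first is the 0.8/0.8 minimum, which belongs to the half of the primary objective concerned with developing the best predictive criteria. The second is the secondary objective of comparing the two index tests. Index test 1 has a scoring algorithm fixed by the earlier consensus study and carries no fitting optimism here, so the comparison leans towards index test 2.

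The safeguard under Minimising bias also does not match the analysis section. What was agreed beforehand is a performance minimum. The diagnostic cut-off itself is determined from the data.

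**Working it through.** **1. The sample.** The plan applies a rule of thumb ("The guidance supports the current rule of thumb for sample size calculations of 10 events per variable") to 16 features: 16 × 10 = 160 cases, and with 1:1 controls 2 × 160 = 320. This reproduces the statement that "a sample size of 160 cases and 160 controls has been calculated". The model, however, starts from 18 candidates, which gives 160 / 18 = 8.9 events per candidate. I use this only to show that the setting is one where optimism is to be expected; the choice of 16 or 18 is a separate matter.

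**2. The data used at each step.** Selection and coefficients: DIPSOC data. Cut-off: ROC curve of that model. Sensitivity and specificity: the study data. AUC comparison: no other data set is named. The result is therefore apparent performance.

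**3. Size of the optimism.** The documents give no feature prevalences, effect sizes, retention p-value or cut-off rule, so all of these are assumptions. Optimism = (value on the study data) − (value of the same frozen rule in new children).

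*Simulation A.* 160 + 160 children; 18 binary features; control prevalences 3% to 20%; 12 features with log odds ratios 0.4 to 1.6 and six with none, all multiplied by a common strength factor; within-group latent correlation 0 with retention at p<0.05, or 0.2 with p<0.10; cut-off at maximum sensitivity + specificity; truth from 20,000 + 20,000 new children; 300 replicates per row.

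| Strength, correlation | AUC study / new | Sensitivity study / new | Specificity study / new | Optimism, Se + Sp | Meets 0.8/0.8: study / new |
|---|---|---|---|---|---|
| 0.7, 0 | 0.748 / 0.697 | 0.657 / 0.603 | 0.732 / 0.685 | 0.101 | 0% / 0% |
| 1.0, 0 | 0.839 / 0.807 | 0.748 / 0.707 | 0.794 / 0.760 | 0.075 | 3% / 0% |
| 1.25, 0 | 0.898 / 0.875 | 0.817 / 0.783 | 0.838 / 0.805 | 0.067 | 53% / 2% |
| 1.25, 0.2 | 0.853 / 0.817 | 0.756 / 0.715 | 0.821 / 0.775 | 0.086 | 8% / 0% |
| 1.5, 0.2 | 0.900 / 0.872 | 0.817 / 0.773 | 0.852 / 0.816 | 0.079 | 57% / 3% |
| 1.5, 0 | 0.941 / 0.925 | 0.873 / 0.840 | 0.881 / 0.855 | 0.059 | 95% / 82% |

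Example, row 1.25, 0: sensitivity 0.817 − 0.783 = 0.034; specificity 0.838 − 0.805 = 0.033; AUC 0.898 − 0.875 = 0.023. Over all ten settings run (four not tabulated), optimism in sensitivity + specificity was 0.06 to 0.10 and in AUC 0.016 to 0.055.

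*Simulation B.* Same sample size; 18 independent features with different assumed prevalences and effects; retention at p<0.05; maximum Youden index, but preferring points where both measures reach 0.8; 400 replicates.

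- Setting 1: AUC 0.876 / 0.839, sensitivity 0.793 / 0.752, specificity 0.814 / 0.780. Optimism 0.037, 0.041 and 0.034.
- Setting 2: AUC 0.895 / 0.869, sensitivity 0.817 / 0.783, specificity 0.824 / 0.790. Optimism 0.026, 0.034 and 0.034.
- Two weaker settings: AUC 0.782 / 0.735 and 0.723 / 0.672. Optimism 0.047 and 0.051.

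The 0.8/0.8 minimum was met on the study data in 46% of replicates in setting 1 and 71% in setting 2.

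**4. The threshold wording.** Minimising bias calls the diagnostic threshold prespecified. Sample size and data analysis has the advisory group setting 0.8/0.8 and the coefficient threshold coming from the ROC curve. Both cannot describe the same quantity.

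**The case against.** **The SAP may deal with it.** Bootstrap or cross-validation is often left to a SAP, and computing performance on the study data is also the first step of a bootstrap correction. This stands in part. A reader might infer that the study has no internal validation; the documents do not support that, because the full protocol and the SAP are not shown. What they do support is that the article names apparent figures as the result and describes no correction.

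**Overestimation is already admitted.** The article calls itself a development study, expects accuracy to be overestimated and asks for external validation. But it attributes the overestimation to case–control design and spectrum bias, not to re-use of the data. The substudy concerns children with indeterminate disease followed up later and does not correct the main figures.

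**The 0.8/0.8 minimum may not be a pass mark.** It can be read as a floor for choosing the operating point, and no consequence of meeting or missing it is stated. This stands. A reader might infer that the study will falsely declare success; no such decision rule is written. Under the floor reading the data are still re-used, and more directly.

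**The bias is small and the pass rates are selected.** The half-width of a 95% interval at 0.8 with 160 children is 1.96 × √(0.8 × 0.2 / 160) = 0.062, larger than 3 to 5 points. True, but optimism shifts the estimate in one direction, and an interval around the shifted value does not show it. The pass rates do depend on where true performance was placed. Gaps such as 53% against 2% arise because true performance was set close to or below 0.8, and Simulation B's cut-off rule raises apparent passes. They are not forecasts for this study.

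**The threshold phrase is loose wording.** Probably so, but it stands as a bias safeguard and should say what was actually fixed.

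**Conclusion.** The concern holds for the article as written. Feature selection, cut-off and accuracy of index test 2 all use the same planned 320 children. The figures set against 0.8/0.8, and those compared with the fixed index test 1, are therefore apparent values biased towards index test 2. The size is moderate: about 3 to 5 percentage points in each of sensitivity and specificity and about 0.02 to 0.055 in AUC. These values rest on assumed prevalences, effects, correlation, retention rule and cut-off rule, though two differently specified simulations agree. The optimism could change the conclusion mainly if true performance is near 0.8. If the features are strong the consequence is smaller (95% of simulated studies meeting the minimum on their own data against 82% on new children). The conflict between the two sections over what was prespecified is visible in the article and does not depend on the SAP.

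**What to change.** In Sample size and data analysis, replace the sentence on applying the criteria to the study data with:

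> *Sensitivity, specificity and AUC of index test 2 will be corrected for optimism by bootstrap with at least 500 resamples. In every resample, backward selection (same prespecified retention rule) and cut-off choice (same prespecified cut-off rule) will be repeated. The 0.8/0.8 minimum and the comparison with index test 1 will be judged on the corrected estimates; apparent values will be shown alongside.*

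The retention rule and the cut-off rule must themselves be written down, or the resampling cannot reproduce the procedure.

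In Minimising bias, replace "a prespecified diagnostic threshold decided with the expert advisory group" with:

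> *a prespecified minimum performance (0.8 sensitivity and 0.8 specificity); the diagnostic cut-off is derived from the data and its performance estimates are corrected for optimism*

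The bootstrap corrects the performance estimates, not the cut-off, and the wording should keep that distinction. If the SAP already provides such a correction, only the alignment of the text is needed.

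Cost: plan wording and some programming, with no extra participants or data. Reported accuracy of index test 2 will be a few points lower, and its advantage over index test 1 may shrink.

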### Secondary objectives

To compare the diagnostic performance of the consensus agreed diagnostic criteria and the best predictive criteria for plaque psoriasis in children and young people.To assess the interobserver variability in the diagnostic criteria assessment.To assess the variability in the reference standard for psoriasis.

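### The planned AUC comparison of the consensus rule with the fitted criteria is tilted towards the fitted criteria, because the fitted criteria are scored on their own development data and possibly in a different form

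*Protocol article*

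**What the plan says.** The first item under Secondary objectives is "To compare the diagnostic performance of the consensus agreed diagnostic criteria and the best predictive criteria for plaque psoriasis in children and young people".

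The Index test section defines the two tests differently. Index test 1 is positive under a rule fixed in advance: "the presence of one or more major criteria or three of more minor criteria would support a diagnosis of psoriasis". The rule belongs to the test itself: "Together these 16 diagnostic features and the scoring algorithm form index test 1". It therefore has one operating point. For index test 2, "These 18 items will be used to create the best predictive criteria using multivariate analysis"; two of those items lie outside index test 1.

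Under Sample size and data analysis, "Multivariate logistic regression analysis will be used to develop the best predictive criteria using the DIPSOC data", by backward selection. The result is drawn as a ROC curve and a cut-off is chosen, with at least 0.8 required for both sensitivity and specificity. The criteria are then run on the study's own data to obtain sensitivity and specificity. Sensitivity and specificity with 95% CIs are also planned for the consensus criteria. The only measure named for comparing the two tests is this: "The performance of the consensus agreed criteria and the best predictive model criteria will be compared using area under the ROC curve".

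The article does not say whether the model enters that comparison as its score or as thresholded criteria, or whether the consensus items enter as the rule or as a count. Further analysis detail is left to a SAP that is not at hand.

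**The concern.** Two features of the comparison push the same way.

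- **Form.** A yes/no rule has a ROC curve made of two straight lines through one point. A score with a concave curve through that same point encloses more area, even though the two tests classify identically at that cut.
- **Data.** The fitted criteria are selected, weighted and cut to suit the participants on whom they are then scored. The consensus rule was fixed before the study and gains nothing from these data.

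At stake is the conclusion on whether the refined criteria improve on the expert rule. A difference in AUC could be reported as better diagnosis when it comes from form and fitting.

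**Working it through.** The article gives no AUC, so there is no stated figure to reproduce.

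**1. Effect of form.** The inputs are the article's operating points: 0.8/0.7 (sensitivity/specificity assumed for the sample size) and 0.8/0.8 (minimum for the best predictive criteria).

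- Yes/no rule: AUC = (Se + Sp)/2.
- Score with an equal-variance binormal curve through the same point (an assumption): AUC = Φ[(z(Se) + z(Sp))/√2].

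| Operating point | As a rule | As a score | Gap |
|---|---|---|---|
| 0.8/0.7 | (0.8 + 0.7)/2 = 0.750 | Φ[(0.842 + 0.524)/1.414] = Φ(0.966) = 0.833 | 0.083 |
| 0.8/0.8 | (0.8 + 0.8)/2 = 0.800 | Φ[(0.842 + 0.842)/1.414] = Φ(1.190) = 0.883 | 0.083 |

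With 160 cases and 160 controls, the standard error of the rule's AUC at 0.8/0.7 is ½√(0.8×0.2/160 + 0.7×0.3/160) = 0.024. The gap is therefore more than three standard errors (0.083/0.024 ≈ 3.5) with no difference at the operating point.

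If the consensus rule sits at 0.8/0.7 and the model at 0.8/0.8, the difference is 0.050 with both as rules (0.800 − 0.750) and 0.050 with both as scores (0.883 − 0.833). In mixed form it is 0.133 (0.883 − 0.750), of which 0.083 is form alone.

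**2. Effect of using the same data.** The planned analysis was simulated with 160 + 160 participants, 18 independent binary features, backward logistic regression with removal at p ≥ 0.05, a cut maximising Se + Sp, and 400 runs. Each fitted model was also applied to a large new sample. The article supplies none of the prevalences; these are assumptions:

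- A: all minor consensus criteria equally informative (0.185 in cases, 0.095 in controls), the major criteria stronger, the two extra items uninformative.
- B: informativeness varies between features.
- C: no feature is informative.

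| Mean AUC | A | B | C |
|---|---|---|---|
| Consensus rule | 0.751 | 0.746 | 0.502 |
| Consensus items as a score (3 per major, 1 per minor) | 0.819 | 0.822 | 0.503 |
| Model score, own data | 0.823 | 0.857 | 0.538 |
| Model score, new data | 0.769 | 0.810 | 0.500 |
| Model thresholded, own data | 0.762 | 0.789 | 0.534 |
| Model thresholded, new data | 0.707 | 0.737 | 0.500 |
| Runs with model score ahead of rule, own data | 100% | 100% | 75.5% |

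Optimism is own data minus new data. For the score it is 0.054, 0.047 and 0.038; for the thresholded criteria 0.055, 0.052 and 0.034. Thresholding removes the form effect but not the optimism.

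In A, comparing the model's score on its own data with the rule puts the model ahead in every run (0.823 against 0.751 on average). Like for like on new data, the consensus criteria are ahead in both forms: 0.819 against 0.769 as scores, and 0.751 against 0.707 as rules. The ranking can therefore be reversed, in a scenario whose equal minor weights suit the consensus rule.

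**3. Score check.** With 3 points per major and 1 per minor criterion, any major criterion gives at least 3. Without one, reaching 3 takes three minor criteria. A cut at 3 or more therefore reproduces the consensus rule exactly.

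**The case against.** The strongest reply is that the article never says a continuous score enters the comparison. Its order of steps is curve, cut-off, application of the criteria, comparison, and that fits two thresholded tests. The 0.083 then disappears. This stands: the form effect is conditional on one reading. The optimism is not, since the criteria are scored on their development data either way.

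A reader might infer something stronger: that the fitted model wins by construction, and that the objective cannot be answered fairly. The document does not support this. Sensitivity and specificity are planned for both tests in participants who all have the same assessment, so the data allow a fair comparison. Those separate figures would also show any trade of sensitivity for specificity that an AUC of two thresholded tests averages away. Nor is a lead guaranteed: with no informative feature the model's score led in about three quarters of runs.

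The form of entry and internal validation may also be settled in the unseen SAP. That limits certainty, but the choice of AUC as the comparison measure is already stated.

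Finally, the article admits that its case–control design and clinic spectrum may inflate accuracy, and that external validation is still needed. Those cautions limit what may be claimed, but they do not address an asymmetry that favours only the fitted test.

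**Conclusion.** The point holds in limited form: the stated comparison is biased towards the fitted criteria. On the natural reading, form adds about 0.08 AUC and same-data optimism is a further tilt of roughly 0.04 to 0.05. If both tests are thresholded, only the optimism remains.

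The 0.08 rests on smooth equal-variance binormal curves, whereas the real score is built from binary items. In simulations A and B the gap between the consensus score and the consensus rule was 0.068 and 0.076. The optimism figures rest on assumed prevalences, independent features, and assumed rules for removal and cut. The direction is better founded than the exact size.

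Severity is moderate. The objective is secondary, the article attaches no superiority margin or decision rule to the AUC comparison, and the study presents itself as developmental.

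**What to change.** State that the two tests are compared in the same form and paired within participants.

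1. Main comparison: the difference in sensitivity among cases and in specificity among controls, each test at its final cut-off, with 95% CIs.
2. Use optimism-corrected figures for the fitted criteria, from a bootstrap that repeats both the backward selection and the choice of cut in every resample. A paired test on the uncorrected classifications is not enough: in simulation A the thresholded model averaged 0.762 on its own data against 0.751 for the rule, but 0.707 on new data.
3. If AUC is kept, either threshold both tests or enter both as scores, again paired and corrected. The 3-and-1 score reproduces the consensus rule at a cut of 3 or more. Its ranking away from that cut is an added assumption, not part of index test 1, and should be labelled so.

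The cost is a change of analysis wording and some computing, using data already collected. The downside is that the new criteria's apparent advantage will shrink.
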